**Grade 1: Mild**
Mild adverse events are asymptomatic or with mild symptoms, or do not require intervention. Such adverse events includeMusculoskeletal pain or injury (asymptomatic or mild)Joint effusion (asymptomatic or mild)Dyspnea with moderate exertionProductive cough with minimal production of sputumWheezing with minimal symptomsDehydration requiring increased oral fluid intakeHypoglycemia or hyperglycemia not requiring medical interventionAsymptomatic hypotension
**Grade 2: Moderate**
Moderate adverse events require minimal, local, or noninvasive intervention, or limit age-appropriate instrumental activities of daily living (preparing meals, doing the groceries, managing money, etc). Such adverse events includeMusculoskeletal pain or injury limiting instrumental activities of daily livingJoint effusion limiting instrumental activities of daily livingDyspnea with minimal exertion limiting instrumental activities of daily livingProductive cough with moderate production of sputum or limiting instrumental activities of daily livingWheezing with moderate symptoms, or requiring medical intervention, or limiting instrumental activities of daily livingDehydration requiring intravenous fluidsHypoglycemia or hyperglycemia requiring intervention but no long-term changes in medical managementHypotension requiring nonurgent interventionChest pain of palpitations related to exertion subsiding with rest
**Grade 3: Severe**
Severe adverse effects are medically significant but not immediately life-threatening, or require hospitalization, or limit self-care activities of daily living (bathing, dressing, using the toilet, feeding self, etc). Such adverse events includeMusculoskeletal pain or injury limiting self-care activities of daily livingJoint effusion limiting self-care activities of daily livingDyspnea at rest limiting self-care activities of daily livingProductive cough with copious production of sputum or limiting self-care activities of daily livingWheezing with severe symptoms limiting self-care activities of daily living, or requiring oxygen therapy or hospitalizationDehydration requiring hospitalizationHypoglycemia or hyperglycemia requiring hospitalization or long-term changes in medical managementHypotension requiring intervention or hospitalizationSyncope
**Grade 4: Life-threatening**
Life-threatening adverse effects require immediate and urgent intervention to avoid death. Such adverse events includeDyspnea (life-threatening) requiring urgent interventionWheezing with life-threatening consequences or requiring urgent interventionDehydration with life-threatening consequencesHypoglycemia or hyperglycemia with life-threatening consequencesHypotension (life-threatening) requiring urgent interventionCardiac arrest
**Grade 5: Lethal**
Lethal adverse effects lead to death and are generally a continuum of life-threatening events. Such adverse events includeDyspnea leading to deathWheezing leading to deathDehydration leading to deathHypoglycemia or hyperglycemia leading to deathHypotension leading to deathCardiac arrest leading to death

#### Second and Third Trials

The second and third trials of the 6MST will be performed in a randomized order, with either direct (therapist present at the home) or remote (therapist present through videoconferencing software, as in a telerehabilitation setting) monitoring. For the remotely monitored trial, another person (ie, family member, etc) will be present to ensure safety in case of emergency. The 6MST and adverse events will be, respectively, performed and collected as in the first trial (the only difference being the presence of the therapist through videoconferencing for one of the trials). The third trial of the 6MST will be followed by a semistructured interview using a guide created a priori. This interview will focus on the 2 themes, that are (1) level of comfort executing the test (ease of execution, symptoms, and anxiety) and (2) perception of safety (regarding test and home and telerehabilitation settings). The interview will be conducted in person or through videoconferencing software, depending on the randomization of the third trial.

### Data Preparation and Analysis

All data will be stored in digital databases (REDCap [Research Electronic Data Capture] in Québec and OpenClinica in France) on secured servers at the participating research facilities (CR-IUCPQ and GHICL) following local protocols. Using a standardized thesaurus, research teams will enter data directly into both databases through remote access. With regard to data analysis, descriptive statistics will be used to summarize participant characteristics. For quantitative data, normality will be verified with Shapiro-Wilk tests and Q-Q plots. All statistical analyses will be completed using SPSS Statistics Version 28 (IBM) with a significance level set at *P*<.05. Graphical analyses will be conducted using Excel (version 2305; Microsoft Corporation) and qualitative analyses will be performed with Nvivio (version 14; Lumivero).

For objective 1, concurrent validity will be assessed using paired sample *t* tests (or Wilcoxon signed-rank tests) to verify whether peak cardiorespiratory (eg, oxygen consumption, minute ventilation, and heart rate) and symptomology (ie, dyspnea and leg fatigue) values obtained during the 6MST are comparable to the CPET and 6MWT. Pearson correlation coefficients (*r*) will also be calculated to quantify the strength of association between peak cardiorespiratory and symptomology values reached during the 6MST with those reached during the CPET and the 6MWT. Additional Pearson correlation coefficients (*r*) will be calculated to determine the strength of the association between the number of steps taken during the 6MST and peak oxygen consumption and heart rate reached during all 3 tests. The level of correlation will be interpreted as poor (≤0.20), fair (0.21-0.40), moderate (0.41-0.60), good (0.61-0.80), and very good (0.81-1.00) [41]. The agreement will be assessed with Bland-Altman plots and 95% limits of agreement (mean difference ± 1.96 SD of the difference) between peak cardiorespiratory and symptomology values reached during the 6MST and those reached during the CPET and the 6MWT [41].

For objective 2, reliability (trial 2 vs 3) will be assessed using paired sample *t* tests (or Wilcoxon signed-rank tests), Bland-Altman plots (with 95% limits of agreement), and intraclass correlations [42-44]. Intraclass correlations will be interpreted as poor (≤0.50), moderate (0.51-0.75), good (0.76-0.9), and very good (0.91-1.00) [44].

For objective 3, all minor and serious adverse events, for all trials, will be reported. The semistructured interviews will be voice-recorded and transcribed. Thematic content analysis will be used to analyze all verbatim [45]. Briefly, a combination of deductive (based on a priori interview guide) and inductive (based on data) approaches will be used to generate themes and subthemes. Coding will be conducted separately by 2 reviewers, who will compare their results and resolve discrepancies through discussion.

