### Objectives and Hypotheses

#### Overview

The overall aim of this project is to provide further evidence regarding the metrological properties of the 6MST in individuals with COPD or ILD. Specific objectives and hypotheses are described below.

#### Objective 1

Objective 1 is to determine concurrent validity and the level of agreement (or bias) between peak cardiorespiratory responses and reported symptomology during the 6MST and CPET and the 6MST and 6MWT. The corresponding hypotheses are that peak cardiorespiratory responses and reported symptomology to the 6MST will be strongly correlated to those measured during CPET and the 6MWT (ie, concurrent validity), and that these values will be systematically lower than those measured during CPET (ie, presence of bias), but similar to those measured during the 6MWT (ie, no bias).

#### Objective 2

Objective 2 is to determine test-retest reliability for the 6MST in home-based settings under direct and remote (ie, videoconferencing) monitoring. The corresponding hypothesis is that measurement error will be minimal and intraclass correlations will be good and similar between direct and remote supervision.

#### Objective 3

Objective 3 is to determine the safety and the perception of the 6MST in individuals with chronic pulmonary diseases in home-based settings under direct and remote monitoring by collecting adverse events and qualitative feedback. The corresponding hypothesis is that the test will be safe (ie, absence of serious adverse events) and individuals will report a good level of overall satisfaction with the test, irrespective of the type of supervision.

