**Exclusion criteria**
Interstitial lung disease associated with connective tissue disease and sarcoidosis (often accompanied by multisystemic effects)Unstable or severe cardiac conditionInvalidating rheumatologic or neurologic conditionWeight exceeding maximal limits of exercise equipment (eg, 130 kg for the stepper)Any other physical or medical condition limiting or contraindicating exercise testingSimultaneous participation in another study requiring changes in medicationRecent pulmonary rehabilitation (≤1 year, potential learning bias for the 6-minute walk test and the 6-minute stepper test)For study 1 only: use of oxygen therapy (unable to provide oxygen therapy during testing due to limitation of gas exchange analysis equipment)For study 2 only: participation in study 1

For study 1, a mean difference of 0.28±0.32 L/min in maximal oxygen uptake between the 6MST and CPET was assumed, based on previous studies between the 6MWT and CPET [22,24]. To detect a difference of this amplitude with a paired sample *t* test, assuming a power of 80%, an α level of .05, and a dropout rate of 15%, 15 participants are needed. Fifteen individuals of each disease population (ie, COPD, n=15; ILD, n=15) will be included for a total sample of 30 participants (Québec, n=15; France, n=15), as cardiorespiratory responses to exercise are different among these populations [25].

For study 2, a minimal acceptable intraclass correlation coefficient of 0.5, and an expected intraclass correlation coefficient of 0.75, were assumed for the test-retest reliability of the 6MST. Assuming a power of 80%, an α level of .05, and a dropout rate of 15%, 52 participants (Québec, n=26; France; n=26) will be recruited. This calculated sample was taken as a whole, as test-retest reliability is not expected to be influenced by the type of respiratory disease.

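### A difference test at P<.05 is assigned to verify that 6MST values are comparable to the 6MWT, with no acceptable bias stated, so the plan cannot establish its own no-bias hypothesis

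*Protocol article*

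**What the plan says.** Objective 1 (Objectives and Hypotheses) makes two opposite predictions. 6MST peak responses and symptoms should be systematically lower than at CPET, "but similar to those measured during the 6MWT (ie, no bias").

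Data Preparation and Analysis applies the same tool to both comparisons. Paired t tests, or Wilcoxon signed-rank tests, are to verify whether peak cardiorespiratory and symptom "values obtained during the 6MST are comparable to the CPET and 6MWT", with significance set at P<.05. Pearson correlations are added. A separate sentence covers agreement: "The agreement will be assessed with Bland-Altman plots and 95% limits of agreement (mean difference ± 1.96 SD of the difference"). Correlations and intraclass correlations receive interpretation bands. The mean bias and the limits of agreement receive none.

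The sample-size text (Participants and Inclusion and Exclusion Criteria) rests on one comparison: "a mean difference of 0.28±0.32 L/min in maximal oxygen uptake between the 6MST and CPET was assumed". It continues: "assuming a power of 80%, an α level of .05, and a dropout rate of 15%, 15 participants are needed". The number is then doubled: "Fifteen individuals of each disease population (ie, COPD, n=15; ILD, n=15) will be included for a total sample of 30 participants", "as cardiorespiratory responses to exercise are different among these populations". No calculation addresses similarity to the 6MWT.

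**The concern.** A paired t test asks whether the data contradict a zero mean difference. It suits the CPET hypothesis. For the 6MWT hypothesis the logic runs the wrong way: the desired finding is the null, and a small or noisy sample makes that finding more likely. A result of P≥.05 is compatible both with no bias and with a bias that matters.

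The Introduction gives a reason to care. It says that different cardiorespiratory responses may raise safety concerns for home use, and that in ILD the 6MST has produced greater heart rate and ventilatory responses than the 6MWT. An unsupported statement of no bias would bear directly on that question. Strengths and Limitations also claims that the sample sizes give sufficient power for the study's objectives. For the 6MWT half of the bias hypothesis, the article shows no calculation behind that claim.

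**Working it through.** **Inputs.** From the sample-size text: planning difference 0.28 L/min, SD of the paired difference 0.32 L/min (both for 6MST versus CPET), power 80%, α .05 (taken as two-sided), dropout 15%, 15 per disease, 30 in total. Not in the article, so assumed: the SD of 6MST minus 6MWT, for which a range of 0.16 to 0.40 L/min is shown, and a true bias of 0.15 L/min for illustration (0.15/0.28 = 54% of the planned CPET gap).

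**1. The plan's own figure.** Standardised difference 0.28/0.32 = 0.875. Paired t power from the noncentral t distribution (df n−1, noncentrality 0.875·√n) is 78.8% at n = 12 and 82.5% at n = 13, so 13 completers are needed. 13 × 1.15 = 14.95, which gives the stated 15. (Dividing by 0.85 gives 15.3, so 16, a trivial difference.) Conversely, 15 × 0.85 = 12.75, about 13 completers per disease and about 26 in all.

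**2. What the test can see at SD 0.32.** The observed mean difference reaches P<.05 only beyond t(0.975, n−1) × SD/√n:
- n = 13: 2.179 × 0.32/√13 = 0.193 L/min
- n = 26: 2.060 × 0.32/√26 = 0.129 L/min

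These are also the 95% CI half-widths.

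**3. Chance that a real bias is non-significant.** This is 1 minus the noncentral-t power, with noncentrality (bias/SD)·√n. At bias 0.15, SD 0.32 and n = 13 the noncentrality is 1.69 and the probability is 66%. At n = 26 it is 2.39 and 37%.

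| SD assumed (L/min) | bias 0.15, n = 13 | bias 0.15, n = 26 |
|---|---|---|
| 0.16 | 13% | <1% |
| 0.20 | 30% | 4% |
| 0.24 | 46% | 14% |
| 0.32 | 66% | 37% |
| 0.40 | 76% | 55% |

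By size of bias at SD 0.32:

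| True bias (L/min) | n = 13 | n = 26 |
|---|---|---|
| 0.10 | 82% | 67% |
| 0.14 | 69% | 43% |
| 0.20 | 46% | 14% |
| 0.28 | 17.5% | 1% |

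At n = 13 the probability crosses one half at a bias of about 0.19 L/min.

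**4. What a proper similarity criterion would deliver.** Declare similarity if the 90% CI lies within ±m, that is |mean| + t(0.95, n−1) × s/√n < m. With zero true bias and SD 0.32 (margins illustrative, not from the article):

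| Margin m (L/min) | n = 13 | n = 26 |
|---|---|---|
| ±0.14 | 6% | 40% |
| ±0.20 | 38% | 85% |
| ±0.28 | 81.5% | 99% |

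**The case against.** The strongest reply is that the t test is not the plan's only evidence on bias. Objective 1 names the level of agreement, or bias, alongside concurrent validity, and the Bland-Altman analysis will show the mean 6MST-6MWT difference and its spread whatever the P value. That stands, and it softens the point. It does not remove it, because the article gives no acceptable bias and no CI criterion by which the displayed difference would count as none.

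Three further limits also stand. The SD of 0.32 belongs to the CPET comparison, which spans two visits 6 to 18 days apart. The 6MST and 6MWT are done at one visit, so their SD may well be smaller. Analysis by disease is inferred from the sizing; the analysis section does not state it. And an acceptable bias could be set in a fuller document that is not shown. None of this makes non-significance evidence of similarity.

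A reader might go further in three ways that the article does not support:
- That it commits to declaring no bias whenever P≥.05. It does not say so; it only gives the test the task of verifying comparability.
- That a large bias would usually be missed. At SD 0.32 and 13 completers this holds only up to about 0.19 L/min; a bias of 0.28 would be missed in 17.5% of studies.
- That the limits, defined as "95% limits of agreement (mean difference ± 1.96 SD of the difference"), are too narrow. This is the conventional Bland-Altman definition and is openly stated. A prediction interval for a new difference is another quantity and an optional refinement.

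**Conclusion.** The point holds in this form: the tool named for comparability with the 6MWT is a difference test, the hypothesis is similarity, and neither the sample size nor the Bland-Altman analysis comes with a criterion that could establish it. The flaw in the inference depends on no number. How often it would mislead depends on the unknown 6MST-6MWT SD and on whether the diseases are pooled. For a true bias of 0.15 L/min the probability of non-significance is 13% to 76% with 13 completers and under 1% to 55% with 26. Those figures assume roughly normal differences, two-sided α .05 and the SD range shown. This should be fixed before analysis. It does not threaten the design or the CPET comparison.

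**What to change.** For the 6MST-6MWT comparison, report the Bland-Altman mean difference in peak oxygen uptake with its 90% and 95% CI. Choose an acceptable bias before analysis, with its clinical rationale. State similar, or no bias, only if the 90% CI lies wholly inside it; otherwise state inconclusive. Say explicitly that P≥.05 will not be read as comparability, for oxygen uptake or for any other peak or symptom value; the latter can be reported as differences with CIs. State whether the comparison is made by disease, pooled or both. Keep the paired t test for CPET, where a difference is hypothesised, and leave the limits of agreement as defined.

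The cost is some rewording and one clinical judgement on the margin, with no extra data. The real price is fewer positive conclusions. With a tight margin most results would be inconclusive: at SD 0.32, 13 completers and no true bias, 94% at ±0.14 L/min and 62% at ±0.20. That is what a sample of this size can support, and the margin should not be widened to avoid it.

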#### First Laboratory Visit

During the first laboratory visit, anthropometric measurements, pulmonary function tests, and CPET on a cycle ergometer will be performed.

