#### Second Laboratory Visit

During the second laboratory visit, spirometry will be repeated to ensure the stability of the participants’ health state (particularly relevant for individuals with COPD). Thereafter, the 6MST and 6MWT will be performed in a randomized order, separated by a rest period of at least 30 minutes.

The 6MWT will be performed in a leveled, unobstructed corridor in accordance with current recommendations [36,37]. Briefly, the 30-meter testing area will be marked at both extremities with brightly colored cones. Standardized instructions will be given before beginning the test, and standardized encouragements will be provided every minute during (see Textbox 3 for instructions in French used in this study) [36]. The total distance traveled will be collected to the nearest meter. Dyspnea, leg fatigue, and cardiorespiratory responses will be collected as described previously.

Standardized instructions and encouragements during the 6-minute walk test. See Multimedia Appendix 2 for the English version.

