### Strengths and Limitations

This research project has strengths and limitations that warrant consideration. With regard to strengths, first, sex parity will be assured and help limit bias, particularly related to the under-representation of people of the female sex in the pulmonary rehabilitation literature [46]. Second, the a priori calculation of sample sizes required will ensure sufficient statistical power to address the study’s objectives. Third, the inclusion of several different and complementary statistical strategies will ensure adequate evaluation of the metrological properties of the included tests. Fourth, the multicenter and multinational nature of this study will improve its external validity and generalizability. Fifth, the inclusion of a mixed methods study design will help ensure that stakeholders (ie, individuals with pulmonary diseases) have input regarding the acceptability and use of the physical tests being validated in this research project. Finally, the publication of this protocol a priori will ensure accountability and any changes made a posteriori will be public knowledge and require justification.

With regard to limitations, first, only individuals with COPD and an ILD will be included in this study. This will limit its generalizability in the population with other pulmonary diseases (eg, asthma and cystic fibrosis). This methodological choice was made in an effort to reconcile feasibility (limited time and budget) and generalizability (ie, heterogeneity). Second, for study 1, participants will be required to perform several physical tests on the same day, potentially leading to fatigue that may alter performances. To address this, tests occurring on the same day are separated by a rest period and are randomized. Moreover, the research team has extensive experience with this type of protocol. Finally, regarding test-retest reliability in study 2, a learning effect is possible as the test will be conducted repeatedly. To limit this effect, the first trial of the test will exclusively serve as a familiarization trial. In addition, a 2-minute warm-up period is allotted before each trial. Nonetheless, as the learning effect may not be completely eliminated, randomization of the second and third trials is performed in order to limit a systemic effect on the test conditions (ie, with a therapist present or through videoconferencing software).

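### Study 1 takes the 6MST-6MWT limits of agreement from raw differences, so any same-day order effect widens them; a cheap refinement is to take the SD from a model with test order

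*Protocol article*

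**What the plan says.** **Design.** In the protocol article, Second Laboratory Visit: "Thereafter, the 6MST and 6MWT will be performed in a randomized order, separated by a rest period of at least 30 minutes". The CPET is elsewhere. Under First Laboratory Visit: "During the first laboratory visit, anthropometric measurements, pulmonary function tests, and CPET on a cycle ergometer will be performed". The randomised order therefore concerns only the 6MST-6MWT pair.

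**Fatigue.** Strengths and Limitations says that in study 1 "participants will be required to perform several physical tests on the same day, potentially leading to fatigue that may alter performances", and answers: "To address this, tests occurring on the same day are separated by a rest period and are randomized".

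**Hypothesis.** Objective 1 expects 6MST values to be lower than those of the CPET, "but similar to those measured during the 6MWT (ie, no bias").

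**Analysis.** Data Preparation and Analysis states that "concurrent validity will be assessed using paired sample" t tests (or Wilcoxon signed-rank tests), with Pearson correlations. For agreement: "The agreement will be assessed with Bland-Altman plots and 95% limits of agreement (mean difference ± 1.96 SD of the difference"). Test order appears in neither the test nor the limits.

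**The concern.** Two tests per person in one session, in randomised order, make a two-period crossover. If the second test of the session runs systematically higher or lower than the first, the 6MST-6MWT difference moves one way in people who step first and the other way in people who walk first. Across the two orders these shifts cancel in the mean, but they add to the scatter.

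Limits of agreement are built from that scatter. An order effect belongs to doing two tests in one session, not to replacing one test with the other, yet the raw SD would count it as disagreement between the tests. Agreement with the 6MWT is half of objective 1.

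The paired test of bias is affected more mildly. Its error variance grows, so it loses power. Because the hypothesis here is no bias, lost power makes the hoped-for non-significant result easier to obtain.

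**Working it through.** **The plan's own figure.** The sample size rests on "a mean difference of 0.28±0.32 L/min in maximal oxygen uptake between the 6MST and CPET was assumed", with 80% power, α of .05 and 15% dropout. A two-sided paired t test needs 13 evaluable participants (power 82.5%; 12 give 78.8%). Then 13 × 1.15 = 14.95, so 15, as stated; 13/0.85 = 15.3 would give 16. The stated 15 is reproduced closely enough. It concerns the 6MST-CPET comparison, which the randomised order does not touch.

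**How an order effect enters the 6MST-6MWT difference.** Let τ be the true mean difference (6MST minus 6MWT), s the SD of the difference without an order effect, and p the shift of the second test relative to the first.

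- 6MST first: difference = τ − p + error
- 6MST second: difference = τ + p + error

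The mean with n₁ people taking the 6MST second and n₂ taking it first is τ + p(n₁ − n₂)/n. The extra term is zero on average under randomisation. The SD with balanced order is sqrt(s² + p²), so the limits widen by the factor sqrt(1 + (p/s)²).

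**Size of the widening.** The documents give no p, so it is an assumed range in units of s. To show L/min, s = 0.32 is borrowed from the CPET assumption, for illustration only.

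| p | p (L/min) | SD (L/min) | Half-width, 1.96 × SD | Widening |
|---|---|---|---|---|
| 0 | 0 | 0.320 | 0.627 | none |
| 0.25s | 0.08 | 0.330 | 0.647 | 3% |
| 0.5s | 0.16 | 0.358 | 0.701 | 12% |
| 0.75s | 0.24 | 0.400 | 0.784 | 25% |
| 1.0s | 0.32 | 0.453 | 0.887 | 41% |

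**What remains in the mean.** With 15 people split 8/7, the leftover is p/15. At p = 0.16 L/min that is 0.16/15 = 0.011 L/min. With unrestricted randomisation of 15, the expected absolute imbalance is 0.21, so the typical shift is 0.21 × 0.16 = 0.034 L/min, in either direction.

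**Type I error of the raw paired test (simulated, n = 15).** With unrestricted order it is 5.0% at p = 0.5s and 5.1% at 1.0s. With 8/7 order it is 3.2% and 0.8%. It is never inflated.

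**Power, illustration only.** This applies the CPET figures 0.28 and 0.32 L/min to a comparison for which they were not stated, with 13 completers and a two-sided 5% test.

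- Unrestricted order, raw versus order-adjusted: about 83% versus 79% at p = 0, 74% versus 79% at 0.5s, and 53% versus 79% at 1.0s.
- Split 7/6, adjusted power about 82% throughout. Raw power at 0.5s, 0.75s and 1.0s is 79%, 72% and 62% if the extra person is in the order that raises the difference. It is about 71%, 58% and 43% if in the other order.

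**The case against.** The strongest reply is that nothing here is misstated. The paired t test and the limits formula are standard, and a journal article may leave an order term to a fuller document that is not shown. This stands in part: the point is not an omission or a contradiction. But the article writes out the SD to be used, and for this comparison a better one is available.

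Second, fatigue is met by design, with at least 30 minutes of rest and random order; familiarisation with both tests limits learning. If the rest works, p is near zero and nothing changes. This stands, and it is why the size is conditional.

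Third, large values of p look implausible. On the borrowed scale, 1.0s is 0.32 L/min, more than the whole 0.28 L/min assumed between the 6MST and the CPET. Sampling error is also large: with 15 people the standard error of a limit is about sqrt(3/15) × s = 0.45s, so its 95% interval is about ±0.96s. A widening of 3 to 12% is small beside that. This stands too, although sampling error averages out over studies and the order contribution does not.

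Fourth, the plan sets no threshold for acceptable limits, so no stated decision turns on this. That is correct.

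A reader might go further and infer that the order effect biases the estimated 6MST-6MWT difference or produces false positives. The design does not support that: the mean is unbiased on average and the raw test holds its level or falls below it. Nor does the point show that study 1 is underpowered, because its power was stated for the CPET comparison.

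**Conclusion.** The point holds in a limited form. The raw SD of the 6MST-6MWT differences absorbs any order effect, and randomised order does not prevent that. The limits widen by 3% at p = 0.25s, 12% at 0.5s and 41% at 1.0s: negligible if the rest period works, material only from about 0.5s.

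This rests on an assumed p, on a constant shift common to all participants, and on near-balanced order. The percentages do not depend on the borrowed 0.32 L/min; the L/min and power figures do, and are illustrative. The CPET comparison is unaffected. This is an inexpensive improvement to a sound standard method, worth specifying before analysis because the protocol itself names the fatigue that would cause it.

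**What to change.** For the 6MST-6MWT comparison only:

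- Regress the within-person difference on test order, coded −1/+1.
- Take the bias as the average of the two order-specific mean differences, and test that.
- Compute the 95% limits of agreement from the residual SD of this model.
- Report the estimated order effect, which also shows whether the rest period did its work.
- Show the unadjusted limits alongside.

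The change needs one variable that the randomisation already produces, and no further participants or procedures. It uses one degree of freedom. If there is truly no order effect, at 13 completers that costs about 1 percentage point of power with balanced order and about 4 with unrestricted order, on the same illustrative inputs.
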